### **7.3 Randomization**

Each study participant will be assigned a unique anonymous identification number, which will be used throughout the study. A block-balanced randomization will be used to determine the order of the interventions. Randomization envelopes will be opened at the admission visit.

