## 6 Study Design

### 6.1 Trial Design

CLASS14 (Closed-loop Assessment Study) is an open-label, randomized, two-way, cross-over study comparing single-hormone (insulin) CLS and sensor-augmented pump therapy in regulating glucose levels for a 12-day period in adults with T1D.

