#### 6.2.2 Exclusion criteria

Subjects who meet any of the following criteria are not eligible for the study:

1. Clinically significant nephropathy, neuropathy or retinopathy as judged by the investigator
2. Recent ( $< 6$  months) acute macrovascular event e.g. acute coronary syndrome or cardiac surgery
3. Warfarin chronic treatment if INR monitoring cannot be evaluated (can increase the risk of bleeding)

4. Chronic use of acetaminophen. Acetaminophen may interfere with glucose sensor readings
5. Pregnancy (ongoing or current attempt to become pregnant)
6. Breastfeeding
7. No nearby party for assistance if needed
8. Plans to go abroad or travel at more than 2 hours distance from Montreal during the trial period
9. Severe hypoglycemic episode within two weeks of screening or during the run-in period
10. Severe hyperglycemic episode requiring hospitalization in the last 3 months
11. Current use of glucocorticoid medication (except low stable dose and inhaled steroids)
12. Known or suspected allergy to the trial products
13. Other serious medical illness likely to interfere with study participation or with the ability to complete the trial by the judgment of the investigator
14. Anticipation of a significant change in exercise regimen between admission and end of the trial (i.e. starting or stopping an organized sport)

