### **7.2 Visit Schedules**

#### **7.2.1 Admission Visit (Visit 1)**

At the admission visit, the following procedures will be taken:

- Inclusion and exclusion criteria will be assessed.
- Subjects will be asked to sign the consent form.
- A medical visit will be taken to establish medical history (i.e. recent severe hypo- and hyperglycemia events, micro- and macrovascular complications, comorbidities, and precise list of all medications).
- A1c level if no recent (< 1 month) result is available.
- Weight, height and waist circumference will be obtained.
- Records of the previous 3 days of insulin therapy will be obtained (total daily dose, carbohydrate to insulin ratios, basal rates).
- Training on the use of the pump and sensor will be provided.
- Subjects will be asked to complete the Diabetes Treatment Satisfaction questionnaire [25].

After the admission visit, the participants will have a run-in period of 12 days using the study sensor. During the run-in period, participants will use their insulin pump. After 6 days ( $\pm 2$  days) and 10 days ( $\pm 2$  days) of the run-in period, an experienced member of the team (nutritionist or nurse) will review the pump and sensor data and will contact study participants to optimize their treatment parameters (insulin to carbohydrate ratios, basal rates, etc) if required. The objective

of this contact is to make obvious therapeutic adjustments (i.e. to address unperceived nocturnal hypoglycemia).

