### **7.2.2 Study interventions (Visit 2 and 3)**

For interventions with the single-hormone CLS, the sensor will be installed at least one day before the start of the intervention by the participants. On the first day of an intervention with the single-hormone CLS, participants will be admitted to the clinical research facility anytime between 8:00 am and 11:30 am. The study insulin pump will be installed and participants will be trained on the closed-loop system, and that includes training on connection and disconnection of the system and meal boluses (a user guide will also be given to participants). Sensor alarm thresholds will be determined by participants. Competency using study devices will be assessed by a team member. Only participants demonstrating competency using study devices will be allowed to continue to the home study phase. Participants will be discharged in the afternoon and advised to continue with study intervention at home for the next 12 days.

On the first day of an intervention with the single-hormone closed-loop system, participants will be asked to activate the exercise mode of the CLS for the following situations: driving for more than 10 minutes, manual work requiring great attention and exercise at moderate or high intensity for more than 30 minutes. On the subsequent days, participants will be asked to measure their capillary glucose level before driving, undertaking manual work requiring great attention or performing an exercise at moderate or high intensity for more than 30 minutes. If the capillary glucose level is below 6.0 mmol/L, participants will need to eat or drink at least 15g of carbohydrates. For all these situations, participants will be asked to measure their capillary glucose level every hour. Participants will be advised to have carbohydrates with them at all times.

For intervention with sensor-augmented pump therapy, the sensor will be installed at least one day before the start of the intervention by the participants. Participants will use their own insulin pump.

For Closed-Loop intervention, participants will be contacted on the first evening to ensure that they have not encountered any unexpected events or technical problems. Additional phone calls will be planned on day 3 and day 9. For the SAPT intervention, participants will be contacted on

Day 3 ( $\pm 2$  days) and Day 9 ( $\pm 2$  days) as they are already contacted on Day 1 for the start of control intervention.

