For both interventions, participants will be asked to record hypoglycemia episodes, calibrations, catheter and sensor changes and hyperglycemic episodes with ketones in a diary provided to them. After each intervention, participants will be asked to complete the diabetes treatment satisfaction questionnaire. This questionnaire will be used to evaluate the impact of, and the satisfaction with study devices.

The first intervention visit will be maximum 30 days after the run-in period. Intervention visits should be separated by 4-40 days. We will have 24-hour technical support available during all interventions.

The duration of each intervention will be 12 days.

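### Section 7.3 opens the sequence envelope before the run-in, so participants are randomised before exclusion 9 is settled and pump settings can be tuned with the order known

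*Protocol*

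**What the plan says.** The time of randomisation is fixed in Protocol Section 7.3: "Randomization envelopes will be opened at the admission visit". What the envelope holds is the order of treatments: "A block-balanced randomization will be used to determine the order of the interventions".

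Section 7.2.1 places the run-in after that visit: "After the admission visit, the participants will have a run-in period of 12 days using the study sensor". At about days 6 and 10 of the run-in, each with a margin of 2 days, a nurse or nutritionist "will review the pump and sensor data and will contact study participants to optimize their treatment parameters".

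Exclusion criterion 9 in Section 6.2.2 reads: "Severe hypoglycemic episode within two weeks of screening or during the run-in period".

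Section 7.2.2 then allows a further gap: "The first intervention visit will be maximum 30 days after the run-in period".

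Section 6.1 says that the trial "is an open-label, randomized, two-way, cross-over study comparing single-hormone (insulin) CLS and sensor-augmented pump therapy". No section says that the order is withheld from the participant or from the staff who review the run-in data.

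**The concern.** Randomisation should come after eligibility is settled and after any preparatory treatment adjustment is finished. Here it comes before both, with two consequences.

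First, anyone who meets criterion 9 during the run-in has already been randomised. The protocol's own rule therefore creates exclusions after randomisation, and each one takes a place out of a block that was balanced when the envelope was opened.

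Secondly, the staff who adjust basal rates and carbohydrate ratios in the run-in may know whether the participant is about to start sensor-augmented pump therapy (SAPT) or the closed-loop system (CLS). If that knowledge changes how far they adjust, first-period control could differ by sequence for a reason other than treatment.

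**Working it through.** The point concerns the order of procedures, and the plan gives no figure for it. The sample size of 36 in Section 8.2 is reproduced by a paired t-test with a 15-point difference, SD 22 in each arm and zero within-person correlation (power 80.3%). It does not depend on when the envelope is opened.

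**Step 1: timeline.** Inputs are from Sections 7.2.1, 7.2.2 and 7.3. Days are counted from the admission visit, assuming that the run-in starts at once.

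| Event | Day |
|---|---|
| Envelope opened | 0 |
| First data review and adjustment | 6 ± 2, so 4 to 8 |
| Second data review and adjustment | 10 ± 2, so 8 to 12 |
| End of run-in | 12 |
| First intervention | 12 to 12 + 30 = 42 |

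Both adjustments fall after the envelope is opened. The order is open for 12 to 42 days before any study treatment.

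**Step 2: eligibility.** Section 7.2.1 lists the check of inclusion and exclusion criteria at admission. Criterion 9 has two parts. The part about the two weeks around screening can be checked then. The part about the run-in cannot be settled before day 12.

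**Step 3: what a shift tied to the known order does to the estimate.** The primary model in Section 8.4.1 has intervention, sequence, period and starting glucose as fixed effects. With complete data, and leaving the starting-glucose adjustment aside, the estimate of CLS minus SAPT is

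½ [(CLS in period 1 − SAPT in period 2) + (CLS in period 2 − SAPT in period 1)],

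where the first bracket comes from the CLS-first sequence and the second from the SAPT-first sequence.

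- Shift of d in period 1 of the SAPT-first sequence only: the second bracket changes by −d, so the estimate changes by −d/2. The sequence and period contrasts also each change by d/2 in size. They take a share of the shift but do not clear it from the treatment contrast.
- Shift of d in both periods of that sequence: the second bracket changes by d − d = 0. The sequence term takes the whole shift and the treatment estimate is untouched.

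Only a shift that differs between the two periods of a sequence matters. The documents give no d. As an assumed range, 2 to 6 points would move the estimate by 1 to 3 points, against the 15-point difference in Section 8.2.

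**Step 4: what lost block balance costs.** The variance of the estimate is proportional to 1/n₁ + 1/n₂, where n₁ and n₂ are the numbers in each sequence. The loss rates here are assumptions, and the 18 per sequence is 36/2.

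- 34 remain (about 5% lost), all losses from one sequence: 1/16 + 1/18 = 0.1181, against 2/17 = 0.1176 if balanced. The ratio is 1.003.
- 32 remain (about 10% lost), all losses from one sequence: 1/14 + 1/18 = 0.1270, against 2/16 = 0.1250. The ratio is 1.016.

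Imbalance of this kind costs very little precision.

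**The case against.** The case for leaving the text alone is substantial.

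- **The cross-over protects the contrast.** The envelope reveals an order, and everyone is meant to receive both treatments. A participant excluded in the run-in contributes no outcome in either period, so the within-person comparison is not distorted selectively. This stands, and it is why the effect is modest.
- **The tuning is limited.** Section 7.2.1 restricts the contacts to evident corrections, with unnoticed night-time lows as the example. The protocol does not say that the reviewing nurse or nutritionist sees the envelope. Section 2 has the algorithm initialised with daily insulin requirements and insulin-to-carbohydrate ratios, so adjusted settings may carry into both arms. This also stands. The text supports saying that settings can be tuned with the order known, not that they will be.
- **Period and sequence are in the model.** This stands only in part. Step 3 shows that they absorb a shift common to both periods of a sequence, but not one confined to a single period.
- **The order becomes known anyway.** In an open-label trial it will be known in the gap before period 1 and between periods. That is true, but both scheduled data reviews for adjusting settings before the first intervention lie inside the run-in, and that is the exposure a later opening removes.
- **The statistical analysis plan may deal with excluded participants.** It may define the analysis sets, but it cannot move the time of randomisation.

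Two stronger readings are tempting, and the documents do not support them. A reader might infer that the early opening costs power. A participant who meets criterion 9 is lost whenever the envelope is opened, the protocol gives no loss rate, and Section 8.2 does not say whether 36 is the number randomised or the number completing. Any loss of power would be a question of dropout allowance.

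A reader might also infer that a later opening would cure the loss of participants who fail the device check on the first CLS day ("Only participants demonstrating competency using study devices will be allowed to continue to the home study phase"). It would not. A SAPT-first participant who fails there leaves SAPT data only, whether the envelope was opened at admission or after the run-in. That is a separate matter.

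**Conclusion.** The point holds in a limited form. The protocol randomises before the run-in part of criterion 9 can be known and before run-in adjustment is finished. Both follow directly from Sections 6.2.2, 7.2.1 and 7.3.

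The consequences are exclusions after randomisation, possible disturbance of the block balance, and an opening for order-aware tuning. A one-period, one-sequence shift of d points would move the treatment estimate by d/2. Neither d nor the number of run-in exclusions can be obtained from the documents, and the cross-over and the limited scope of the adjustments make a large effect unlikely. The text does not show that the primary result would be biased. This is a low-cost improvement to the design, not a must-fix.

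**What to change.** Amend Section 7.3 so that the envelope is opened after the run-in, once criterion 9 has been confirmed as not met and the last run-in adjustment of settings has been made, and before the first intervention is booked. The sample size and the model stay as they are.

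The cost is one sentence by amendment. The order is learned 12 days later, so intervention visits are booked about two weeks later than now. The existing window of up to 30 days after the run-in leaves room for this. The order would then be open for 0 to 30 days before the first intervention in place of 12 to 42. The change works only for participants not yet admitted, since an envelope once opened cannot be closed again.

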## **8 Statistical Analysis**

### **8.1 Study Endpoints**

#### **8.1.1 Primary endpoint**

Percentage of time of glucose levels spent in the target range (3.9-10.0 mmol/L).

#### **8.1.2 Secondary endpoints**

1. Percentage of time of glucose levels spent *a.* between 3.9 and 7.8 mmol/L; *b.* below 3.9 mmol/L; *c.* below 3.3 mmol/L; *d.* below 2.8 mmol/L; *e.* above 10.0 mmol/L; *f.* above 13.9 mmol/L; *g.* above 16.7 mmol/L.
2. Percentage of time (00:00-6:00) of glucose levels spent *a.* below 3.9 mmol/L; *b.* between 3.9 and 7.8 mmol/L; *c.* between 3.9 and 10.0 mmol/L; *d.* below 3.3 mmol/L; *e.* below 2.8 mmol/L; *f.* above 10.0 mmol/L; *g.* above 13.9 mmol/L; *h.* above 16.7 mmol/L.

3. Mean glucose levels.
4. Fasting sensor glucose levels.
5. Standard deviation of glucose levels and insulin delivery.
6. Coefficient of variance of glucose levels and insulin delivery.
7. Between-day variability in glucose levels and insulin delivery.
8. Total insulin delivery.
9. Number of hypoglycemic events less than 3.1 mmol/L (>20 minutes).
10. Number of nights with hypoglycemic events less than 3.1 mmol/L (>20 minutes).
11. Number of days with hypoglycemic events less than 3.1 mmol/L (>20 minutes).
12. Total number of hours and percentage of time of sensor availability.
13. Time (hours) between failures due to sensor unavailability.
14. Time (hours) between failures due to pump connectivity.
15. Number of days with at least one technical problem.
16. Number of hours and percentage of time when patients switched back to sensor-augmented pump therapy.
17. Number of hours and percentage of time when the CLS was automatically switched to sensor-augmented pump therapy.
18. Number of calls and patients calling for technical issues related to CLS.

## **8.2 Sample Size and Power Calculations**

The required sample size to obtain a power of 80% to detect a difference of at least 15% in the percentage of time of glucose levels spent in the target range between with single-hormone CLS and sensor-augmented pump therapy, under a paired design, assuming a common SD of 22% in each arm, and a two-sided Type I error ( $\alpha$ -level) of 5%, is 36 patients. Calculations were done using SAS 9.4 power procedure.

## **8.3 Level of Significance**

5% significance threshold will be used to declare statistical significance.

## **8.4 Statistical Tests**

### **8.4.1 Primary endpoint analysis**

The primary endpoint for this study is percentage of time of glucose levels spent in the target range (3.9-10.0 mmol/L), and will be compared between single-hormone CLS vs. sensor-

augmented pump therapy. To estimate the difference between the two interventions on the primary endpoint, we will use a linear mixed effect model (LMEM) with the intervention, treatment sequence, period, and starting glucose entered as fixed effect covariates and subject nested within sequence as random effect. The model is suited for repeated observations, i.e., adjusts for patient-level intra-correlation. Residual values will be examined for normality. Because time in target data have positive values that can follow a non-normal distribution, non-parametric bootstrap procedures will be used to estimate parameters and their 95% confidence interval as a sensitivity analysis.

#### **8.4.2 Secondary endpoint analysis**

A similar statistical strategy employed for the analysis of the primary endpoint will be used to compare treatment effects for all continuous secondary outcomes. Significance level is set at 5%. Sensitivity analysis, including non-parametric bootstrap method and zero-inflated model will be adopted following the distribution of the data.

Hypoglycemic episode and other count variables will be compared among intervention using a linear mixed effect model with Poisson family (or negative binomial), adjusted for intervention, sequence, and period as fixed effect and individuals as random effect.

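### Sections 8.3 and 8.4.2 apply an unadjusted 5% significance rule to 27 to 29 secondary comparisons, with no hierarchy or exploratory label

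*Protocol*

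**What the plan says.** Section 8.3 gives one rule for the whole trial: "5% significance threshold will be used to declare statistical significance". It does not restrict the rule to the primary endpoint.

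Section 8.4.2 carries the rule over to the secondary endpoints. It commits to "compare treatment effects for all continuous secondary outcomes" with a strategy similar to that for the primary, and then says "Significance level is set at 5"%. It adds that "Hypoglycemic episode and other count variables will be compared among intervention", using Poisson or negative binomial mixed models.

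Section 8.1.2 lists 18 numbered secondary items, several with many parts. Item 1 has seven whole-day glucose ranges. Item 2, "Percentage of time (00:00-6:00) of glucose levels spent", has eight. The protocol does not rank the items, name a key secondary, make any test depend on the primary result, adjust for multiplicity or describe the secondary analyses as exploratory.

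**The concern.** A protocol that said nothing about multiplicity could leave it to the statistical analysis plan. This one states a rule for declaring significance and repeats it for the secondary endpoints. An analysis plan that adjusted these tests, or made them exploratory, would have to depart from the protocol's text.

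On its plain reading the 5% applies to each comparison. The set of claims it permits has a much higher error rate, and nothing tells a reader of the results how to weigh one isolated p-value below 0.05.

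Hypoglycaemia shows the problem most clearly. Section 1 stresses reduced hypoglycaemia in earlier closed-loop trials, and section 3.6 anticipates a risk equal to or lower than under sensor-augmented pump therapy. Section 8.1.2 then measures hypoglycaemia in nine ways: three whole-day thresholds, the same three at night, and counts of events, nights and days below 3.1 mmol/L. The protocol does not say which of the nine would carry a claim.

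**Working it through.** **Related figure in the plan.** The protocol states no error rate for the secondary set. Its only error calculation is the primary sample size in section 8.2: 15 percentage points, SD 22 in each arm, paired, two-sided 5%, 80% power, 36 patients. With zero within-patient correlation (an assumption; none is stated) the SD of the difference is 22 × √2 = 31.1. The exact paired t-test then has 80.3% power at 36 patients and 79.1% at 35, so 36 is reproduced. This calculation covers one test and does not involve the secondary endpoints.

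**Count of between-arm comparisons (section 8.1.2).**

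| Items | Content | Comparisons | Running total |
|---|---|---|---|
| 1 | Whole-day ranges a–g | 7 | 7 |
| 2 | Night ranges a–h | 8 | 15 |
| 3, 4 | Mean glucose; fasting glucose | 2 | 17 |
| 5, 6, 7 | SD, CV and between-day variability, each for glucose and insulin | 6 | 23 |
| 8 | Total insulin | 1 | 24 |
| 9–11 | Hypoglycaemic events, nights, days | 3 | 27 |
| 12 | Sensor availability, hours and percent | 2 | 29 |

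Items 16 to 18 have no counterpart in the control arm and are left out. Items 13 to 15 are technical and are also left out. Adding item 13 would give 30 comparisons and would not change the conclusion.

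**Expected false positives if CLS changes none of them.** k × 0.05, whatever the correlation: 27 × 0.05 = 1.35 and 29 × 0.05 = 1.45.

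**Chance of at least one, independent tests.** 1 − 0.95^k: 1 − 0.95^27 = 0.750 and 1 − 0.95^29 = 0.774. For two-sided tests with jointly normal statistics, Šidák's inequality makes this an upper limit whatever the correlation.

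**Chance of at least one, correlated tests.** The protocol gives no correlation between the test statistics, so a common value r is assumed and varied. Each statistic is normal and is compared with ±1.96.

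| Assumed r | 27 tests | 29 tests |
|---|---|---|
| 0 | 75% | 77% |
| 0.3 | 63% | 65% |
| 0.5 | 48% | 50% |
| 0.7 | 33% | 33% |
| 0.9 | 17% | 17% |

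**Illustrative check.** Sensor traces were simulated for 36 patients, two periods and 12 days with no treatment effect, and analysed by paired t-tests. All parameters were assumed; there were four settings of 600 runs each. The chance of at least one false positive was 43–46% for 27 endpoints and 45–50% for 29. When any occurred there were about three on average, because overlapping endpoints tend to reach significance together.

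**Benefit direction only.** Counting errors in one direction at 2.5% each, independence gives 1 − 0.975^27 = 49.5% and 1 − 0.975^29 = 52.0%, with 27 × 0.025 = 0.68 to 29 × 0.025 = 0.73 expected.

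**The nine hypoglycaemia measures alone.** 1 − 0.95^9 = 37% if independent, 27% at r = 0.5 and 20% at r = 0.7, counting both directions.

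**The case against.** **Analysis plan.** Ordering and multiplicity control are often left to an analysis plan, which may exist and could add them. A 5% level per comparison is neither false nor contradictory, and the protocol never says that 5% is the error rate of the whole set. This limits the point but does not remove it, because the protocol itself fixes the threshold for declaring significance.

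**Likelihood.** From the 75–77% a reader might infer that at least one false claim is likely. The documents do not support that, because the figure needs independence. The thresholds in section 8.1.2 are nested, the night is part of the whole day, event counts overlap with days and nights with events, and the two sensor-availability measures express one quantity. Under plausible correlation the chance can fall below one half.

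**Direction.** A reader might also take the whole figure as the risk of a false benefit. Only about half of it lies in that direction, and some measures, such as insulin variability and sensor availability, are not evident benefits at all.

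**Standing.** A reader might infer that secondary results rank equally with the primary. The protocol does not say so. Its objective, hypothesis, primary endpoint and sample size all concern time in 3.9–10.0 mmol/L.

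**Scenario.** Time below 3.9, within 3.9–10.0 and above 10.0 mmol/L add to 100%. If CLS changed no secondary endpoint, the primary would be unchanged too and its test would be non-significant in about 95% of trials. A stray secondary result would therefore usually appear beside a negative primary. That is correct, but the stated rule has no gate to stop such a result from being declared significant.

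**Count.** The upper figure of 29 is soft, because section 8.4.2 does not clearly say that sensor availability is compared between arms. The 27 is firm.

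**Conclusion.** The point holds in a limited form. The protocol permits significance claims on 27 secondary comparisons, possibly 29, at an unadjusted 5% each. The 1.35 to 1.45 expected false positives do not depend on correlation, but they do assume that CLS affects none of these outcomes; if some effects are real, only the remaining comparisons contribute. The chance of at least one false positive is substantial rather than established as likely. The 33–65% range rests on assumed common correlations of 0.7 to 0.3, and even at 0.9 the chance is 17%, more than three times 5%.

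The primary test keeps its two-sided 5% level, so the trial's main conclusion is not at risk. The weakness is confined to what may be claimed on hypoglycaemia and the other secondary endpoints. The change is worth making because it is cheap.

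**What to change.** In sections 8.3 and 8.4.2, restrict the term statistical significance to the primary endpoint. State that secondary endpoints will be reported as estimates with 95% confidence intervals, labelled exploratory and unadjusted for multiplicity.

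If the sponsor wants one confirmatory secondary claim, for instance on hypoglycaemia, name that single endpoint before the data are seen and test it at 5% only if the primary is significant. This fixed sequence keeps the error rate over the two confirmatory claims at 5%.

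The cost is about two sentences, with no extra patients or data and no change in power for the primary endpoint. The downside is that the other secondary results cannot be called statistically significant, however small their p-values.

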### **3.4 Risks associated with participation in the study**

**Hypoglycemia:** Even though the efficacy of the CLS to reduce the occurrence of hypoglycemia has been shown, it is always possible that participants might experience hypoglycemic episodes during the 12-day intervention. Participants will be recommended to treat hypoglycemia according to guidelines: consume 15g of carbohydrates if capillary glucose is below 4 mmol/L or if they have symptoms of hypoglycemia. They will be recommended to measure capillary glucose 15 minutes later and repeat treatment if glucose levels are still below 4 mmol/L or if they still have symptoms of hypoglycemia. If they treat 5 or more hypoglycemic episodes (capillary glucose < 4.0 mmol/L) in one day, they will be asked to contact the research team. If they experience a severe hypoglycemia event (third party assistance is necessary to treat hypoglycemia), they will be asked to immediately end the study intervention and to contact the research team. Patients will be reminded about risk factors for hypoglycemia, symptoms and

treatment. In addition, patients will be asked to always have carbohydrates available and if they do not own an intact glucagon kit, one will be provided and they will be asked to keep it with them during the entire trial.

**Hyperglycemia:** Even though the efficacy of the CLS in reducing the occurrence of hyperglycemia has been shown, it is always possible that participants might experience hyperglycemic episodes during the 12-day intervention. Participants will be instructed to measure blood ketones levels when capillary glucose is above 16 mmol/L for at least one hour. If blood ketones are above 1.5 mmol/L, it will be important to take necessary actions to correct the situation. These measures include: an insulin correction bolus, proper hydration, changing the insulin infusion set and/or insulin reservoir and eventually delivering a bolus of insulin with a syringe or insulin pen. Participants will be asked to monitor glucose levels and blood ketones levels and to have regular contact with the research team upon resolution of hyperglycemia and ketonemia. If the situation is not resolved within 6 hours, participants will be asked to prematurely end the intervention. The procedure for ketone management is described in detail in Annex A.

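### The count model for hypoglycemic events, nights and days names no exposure term, although sensor gaps and early stops can make observed time unequal between the two interventions

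*Protocol*

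**What the plan says.** Section 8.4.2 gives the count model as "Hypoglycemic episode and other count variables will be compared among intervention using a linear mixed effect model with Poisson family (or negative binomial"). The same sentence goes on to list the terms of that model, and the list reads "adjusted for intervention, sequence, and period as fixed effect and individuals as random effect". It names no offset, rate or denominator.

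Section 8.1.2 defines the outcomes as totals. Item 9 is "Number of hypoglycemic events less than 3.1 mmol/L (>20 minutes"), item 11 is "Number of days with hypoglycemic events less than 3.1 mmol/L (>20 minutes"), and item 10 is the same for nights. By contrast, the primary endpoint and items 1 and 2 are percentages of time.

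Three places bear on observed time:

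- Section 7.2.2 fixes each intervention at 12 days, and section 2 provides two sensors for each, so planned exposure is equal.
- Section 8.1.2, item 12, makes sensor coverage an endpoint in its own right: "Total number of hours and percentage of time of sensor availability".
- Section 3.4 has two early-stop rules. After severe hypoglycemia, participants hear that "they will be asked to immediately end the study intervention and to contact the research team". Hyperglycemia with ketonemia that is not resolved within 6 hours also ends the intervention. Neither rule is limited to one arm.

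**The concern.** A sensor-defined event can be counted only while the sensor reports and the intervention is running. A log-link model of totals with no exposure term compares expected totals, not rates. The random individual effect does not repair this, because observed time can differ between the two periods of the same person. The period effect absorbs a loss common to a period, not one that follows the intervention.

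If one intervention is observed for less time, its total falls in proportion and it looks safer with no true difference. Early stopping gives this an awkward direction. A severe hypoglycemia cuts short the intervention in which it happened, and the model does not know that the remaining days were never observed. At stake is the between-arm comparison of hypoglycemic event counts in an open-label study that, by section 1, precedes a planned trial in 100 adolescents and adults.

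**Working it through.** **Inputs from the protocol.** 36 participants (section 8.2), crossover, 12 days per intervention, two-sided 5% level. The protocol states no power, event rate or exposure figure for the count endpoints. Its one sample-size figure, 36 for the primary endpoint, reproduces with a paired t-test at zero within-person correlation: SD of the difference 22 × √2 = 31.1, difference 15, power 80.3%. It does not bear on the count model and serves here only as the number of participants.

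**Assumed inputs.** Mean events per participant per 12 days, λ = 2, 4 or 8. Exposure ratio r (observed time in one intervention divided by the other) = 1.00, 0.98, 0.95 or 0.90. True rate ratio 1. Poisson counts given the person, with a log-normal person effect of SD 0.7.

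**Step 1, the estimand.** With rate ratio θ, the expected totals are 36λθr and 36λ. The model without an offset therefore estimates θ × r. With θ = 1, the apparent ratio is r.

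**Step 2, error under a true null, by formula.** For a comparison of two totals within person, the shift of the z statistic is about

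δ = √(36λ) × (1 − r) / √(1 + r).

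Example: λ = 4, r = 0.90 gives 12 × 0.10 / 1.378 = 0.87. The two-sided rejection rate is Φ(−1.96 + 0.87) + Φ(−1.96 − 0.87), about 14%.

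**Step 3, simulation.** 20,000 trials per setting, with a conditional test of the two totals:

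| Exposure ratio | λ = 2 | λ = 4 | λ = 8 | With exposure term |
|---|---|---|---|---|
| 1.00 | 4.8% | 4.9% | 5.1% | 4.8-5.1% |
| 0.98 | 5.1% | 5.3% | 5.5% | 5.0-5.1% |
| 0.95 | 5.8% | 7.2% | 9.6% | 5.0-5.1% |
| 0.90 | 9.3% | 13.8% | 22.7% | 4.7-5.0% |

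The formula agrees within 1 percentage point in every unequal-exposure cell.

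**Step 4, what early stops alone would do.** Planned exposure per intervention is 36 × 12 = 432 days. One participant stopping at day 6 in one arm only gives 426/432 = 0.986. Four such stops give 408/432 = 0.944. These ratios treat those who stop as having an average event rate. If their rate is higher, more of the expected total is lost than the ratio shows.

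**Step 5, what sensor gaps would have to be.** A ratio of 0.90 with full coverage in the other arm means a loss of 0.10 × 12 = 1.2 days per participant on average. A ratio of 0.98 means 0.24 days.

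**The case against.** The strongest reply is that the design is balanced: same duration, same sensors, same stopping rules. A reader might infer that observed time does differ between the arms. The protocol does not say so. Item 12 measures availability but predicts no imbalance. The part-day at the facility followed by the words "advised to continue with study intervention at home for the next 12 days" might suggest a longer closed-loop period, but section 7.2.2 also fixes the duration at 12 days. Even if an assumed quarter to half day were added, that is 0.25/12 to 0.5/12, about 2-4%, and it would lengthen closed-loop exposure. Larger imbalances can be simulated (a ratio of 0.80 gives 24-72%), but nothing in the document supports them.

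A second reply is that silence is not exclusion, and an analysis plan that is not shown may specify an offset. That is fair. Nor does the protocol say that unobserved days are counted as event-free, since it does not describe how incomplete periods are handled. What remains is that section 8.4.2 lists the model's terms and section 8.1.2 fixes the outcomes as numbers. Adding an offset changes the estimated quantity from a ratio of totals to a ratio of rates, so it is more than a missing detail.

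Third, it would be wrong to infer that hypoglycemia is hidden. Items 1b-d and 2a, d and e are percentages of time, and section 10 calls a safety board meeting after a serious adverse event such as severe hypoglycemia. This limits the consequences to the count comparisons. Finally, item 8, "Total insulin delivery", is continuous, lies outside the count model and does not depend on sensor uptime. It is affected only if it is summed over a shortened period, and the protocol does not state the unit.

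**Conclusion.** The point holds conditionally. As stated, the count model has no exposure term, and its ratio equals the rate ratio multiplied by the ratio of observed time. With equal observed time there is no bias and the error is about 5%. At an exposure ratio of 0.98 the effect is negligible (about 5-6%). At 0.95 the error is about 6-10%, and at 0.90 about 9-23%, with apparent ratios of 0.95 and 0.90 and no true difference.

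The proportionality follows from the log-link model. The error rates rest on the assumed event rates and exposure ratios, Poisson variation within person and 36 completed pairs. Extra within-person variation handled by a negative binomial model would lower the error rates but not the bias in the ratio. A few early stops alone would move the result little. This is a cheap improvement, not a demonstrated error in the trial's safety conclusions.

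**What to change.** In section 8.4.2:

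- For item 9, add log(hours of available sensor data in that period) as an offset.
- For items 10 and 11, use observed nights or observed days as the denominator, and state beforehand how much sensor data makes a night or day observed. Sensor hours suit these less well, because the counts are bounded by the nights or days observed.
- For other counts compared between arms, such as days with a technical problem (item 15), use observed intervention days.
- Report rates rather than totals, and express item 8 per observed day.

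The cost is a few sentences, and sensor hours are already collected as item 12. If observed time proves equal, the results do not change. There is one limit: an offset corrects for the amount of lost time, not for time lost because of the outcome itself. Early stops and their reasons should therefore be reported by arm next to the rates.
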